#### Treatment motivation and therapeutic alliance for CR/Active control condition

Following the completion of each cognitive remediation or active control visit, participants will complete the Intrinsic Motivation Inventory (Choi et al. 2010) and the Session Rating Scale (Duncan et al. 2003) to assess their motivation to participate in CR and their alliance with the clinician delivering the intervention, respectively.

### Proposed analyses

Prior to the analyses, data will be screened for outliers and departures from a normal distribution. Data analyses will be completed using an “intention-to-treat” principle (Montori & Guyatt 2001). Consequently, data from all participants will be included in the analyses regardless of their level of participation in study interventions over the course of the project. Per existing statistical guidelines (Collins et al. 2001; Graham 2009), missing data will be estimated using multiple imputation (Rubin 1987).

The interaction between time (i.e., baseline vs. 6-month) and treatment condition (DCS vs. placebo) on our primary outcome variable (MCCB composite cognition score) will be assessed using a repeated measures ANOVA. An a priori estimate of statistical power was completed using G*Power 3.1 (Faul et al. 2009). Assuming a correlation greater than or equal to 0.40 between baseline and six month MCCB composite cognition scores and a medium effect size (i.e., *f* = 0.25), the power to detect a statistically significant interaction between time and treatment condition (i.e., cycloserine/placebo) is greater than or equal to 0.80. Should we find a statistically significant time X treatment condition interaction, post-hoc probing of the interaction will be completed using t-tests with Bonferroni corrections to maintain an alpha of 0.05.

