### Primary outcome measure: change in global cognitive functioning

Cognitive functioning among study participants will be assessed at baseline and 6-month follow-up using the MATRICS Consensus Cognitive Battery (MCCB: (Nuechterlein et al. 2008)). For this study, the primary outcome measure will be change in the MCCB global cognition composite score from the baseline to 6-month assessment.

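### The primary time-by-treatment ANOVA is valid and powered as stated, but it is a change-score t-test; adjusting for the baseline MCCB already collected would be more precise at no data cost

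*Protocol article*

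**What the plan says.** The section on the primary outcome measure states that "the primary outcome measure will be change in the MCCB global cognition composite score from the baseline to 6-month assessment". It also fixes when the battery is given: "Cognitive functioning among study participants will be assessed at baseline and 6-month follow-up using the MATRICS Consensus Cognitive Battery". A baseline score is therefore planned for every participant.

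The Proposed analyses section names the effect to be tested: "The interaction between time (i.e., baseline vs. 6-month) and treatment condition (DCS vs. placebo"). The outcome and method follow: "MCCB composite cognition score) will be assessed using a repeated measures ANOVA". No baseline covariate is named. The power statement in the same section rests on a lower bound for the correlation ("Assuming a correlation greater than or equal to 0.40 between baseline and six month MCCB composite cognition scores") and on "a medium effect size (i.e., *f* = 0.25"), and concludes that power ("i.e., cycloserine/placebo) is greater than or equal to 0.80". The Participants section gives a sample of about 40, and the randomization section gives 1:1 allocation.

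**The concern.** With only two visits and two arms, the repeated measures model has nothing to model beyond each participant's change. Its interaction test uses the baseline score by subtracting it in full, as if the slope of the 6-month score on baseline were 1. At the protocol's own planning correlation, with equal variances, that slope is 0.40. Subtracting the whole baseline therefore over-corrects and adds noise that a fitted slope would remove.

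Precision is at stake. At the planning values, power is only just above 0.80 with 40 participants, and the analysis gives up information that is already being collected.

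**Working it through.** **Inputs.** From the protocol: N about 40, so 20 per arm (Participants; 1:1 randomization); correlation ρ at least 0.40, f = 0.25 and power at least 0.80 (Proposed analyses). Assumed here: two-sided α = 0.05 for the primary test (the protocol states 0.05 for the post-hoc tests), equal variance σ² at both visits, a common slope in both arms, and no dropout. Results are in units of σ.

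**1. Reproducing the stated power.** For the within-between interaction with m = 2 visits:

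λ = f²·N·m/(1 − ρ) = 0.0625 × 40 × 2 / 0.60 = 8.33, with 1 and 38 degrees of freedom.

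The noncentral F distribution gives power 0.803. The protocol's figure is confirmed. With 38 participants power is 0.782, so 40 is the smallest even total that reaches 0.80.

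**2. The planned test is a change-score t-test.** In a 2 × 2 layout a between-arm difference in change of D produces cell interaction terms of ±D/4. So f = D/(4σ), and f = 0.25 means D = 1.0 SD. The variance of a change score is 2(1 − ρ) = 1.20. A two-sample t-test with D = 1.0, variance 1.20 and 20 per arm has power 0.803, the same figure. In 200 simulated data sets the interaction F and the squared change-score t differed by no more than 4 × 10⁻¹⁴.

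**3. Variance under each analysis.** The treatment estimate has variance (4/N) times a factor:

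- change score: 2(1 − ρ)
- ANCOVA: (1 − ρ²) × [1 + 1/(N − 4)], where the bracket is the cost of estimating the slope; at N = 40 it is 1 + 1/36 = 1.028.

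At ρ = 0.40 these are 1.20 and 0.84 × 1.028 = 0.863. The ratio is 0.72, a reduction of about 28%. A simulation of 40,000 trials gave 28.2%. The large-sample figure, without the bracket, is 30%.

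| ρ | Change-score factor | ANCOVA factor | Reduction | Power, D = 1.0: change → ANCOVA |
|---|---|---|---|---|
| 0.4 | 1.20 | 0.863 | 28% | 0.80 → 0.91 |
| 0.6 | 0.80 | 0.658 | 18% | 0.93 → 0.97 |
| 0.7 | 0.60 | 0.524 | 13% | 0.98 → 0.99 |
| 0.8 | 0.40 | 0.370 | 7.5% | 0.998 → 0.999 |

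The ratio of the two factors is 1.028 × (1 + ρ)/2. It reaches 1 at ρ = 2/1.028 − 1, about 0.95. Above that, ANCOVA gains nothing at this sample size.

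**4. A smaller effect.** For D = 0.5 SD, power moves from 0.29 to about 0.38 at ρ = 0.4, and from 0.68 to 0.72 at ρ = 0.8.

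**5. Confidence interval half-width at ρ = 0.4.** Change score: 2.024 × √(1.20 × 0.1) = 0.70 SD. ANCOVA: 2.026 × √(0.863 × 0.1) = 0.60 SD.

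**6. Where the gain comes from.** The change-score estimate moves by −(1 − ρ) = −0.60 per unit of chance baseline difference (simulated slope −0.600; under ANCOVA 0.000). With 20 per arm that difference has standard deviation √(2/20) = 0.316, so a one-standard-deviation imbalance moves the estimate by 0.6 × 0.316 = 0.19 SD. The variance this contributes is 0.19² = 0.036. The total variance of the change-score estimate is 1.20 × 0.1 = 0.12, and 0.036/0.12 = 0.30. This is exactly the large-sample reduction in step 3.

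**The case against.** The strongest reply is that nothing in the document is wrong. Change is the declared outcome, the interaction tests change, the test keeps its type I error and is unbiased over randomization, and the power claim reproduces. All of this stands, so the point is an improvement and not the correction of an error.

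The second reply is that 0.40 is a floor and the gain is greatest there. This also stands. At a correlation of 0.7 or more, power for the planned effect is already 0.98 and has little room to rise; the benefit there is mainly a somewhat narrower interval.

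Four stronger readings are tempting, and the documents do not support them:

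- **Bias from baseline imbalance as a further harm.** The shift in step 6 is conditional on the imbalance observed. It averages to zero over randomization and is already inside the change-score standard error. It is the same gain seen from another side.
- **Easier pooling after multiple imputation.** The planned interaction has one degree of freedom and is itself a mean difference with a standard error. It pools by Rubin's rules just as an ANCOVA coefficient does.
- **ANCOVA can never be less precise.** That holds only in large samples; see the crossing point near 0.95.
- **Randomization is unstratified, so imbalance is likely.** The article does not mention stratification, but a condensed article may leave that to the full protocol. The argument does not need it.

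**Conclusion.** The planned primary analysis is sound and correctly powered on its own assumptions, but it is not the most efficient use of the data. With 40 participants, ANCOVA on baseline MCCB would reduce the variance of the treatment estimate by about 28% at the protocol's minimum correlation, falling to 7 to 8% at 0.8 and to essentially nothing above about 0.95. At the minimum correlation the gain in power for the planned 1.0 SD difference is about 11 percentage points, and the interval half-width shrinks by about 0.1 SD.

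These figures assume equal variances at the two visits, a common slope and complete data. The protocol gives no dropout rate, and none was assumed. The actual correlation is unknown, so the gain should be quoted as a range and not as its value at 0.40.

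**What to change.** Replace the repeated measures ANOVA sentence in Proposed analyses with a linear model of the 6-month MCCB composite on treatment arm and baseline MCCB composite, fitted in each imputed data set and pooled. Report the adjusted between-arm difference with its 95% confidence interval and p-value. The outcome definition can stay as change, because regressing change on arm and baseline gives the identical treatment coefficient. Make the change before unblinding, so that it is prespecified.

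The cost is one sentence of text and one residual degree of freedom (37 in place of 38). No new data are needed. The existing power statement may be kept as it is; at the correlations considered here (0.4 to 0.8) it would be conservative for the adjusted analysis.

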**Participant flow and study design.**

### Participants

Approximately, forty individuals with bipolar disorder will be recruited to participate in this study. Eligibility criteria include (i) diagnosis of Bipolar I or Bipolar II disorder as determined per the Structured Clinical Interview for the DSM-IV (First et al. 2002); (ii) ages 18–65; (iii) premorbid IQ greater than or equal to 70 as estimated by the reading subtest of the Wide Range Achievement Test (Wilkinson & Robertson 2006); (iv) ability to provide informed consent; (v) fluency in English per self-report from the participant; (vi) current remission of depressive symptomatology as indicated by a score of 8 or less on the Bipolar Depression Rating Scale (Berk et al. 2007); (vii) current remission of manic symptoms as indicated by a score of 7 or less on the Young Mania Scale (Young et al. 1978); and (vii) agreement to use at least one form of birth control during study participation. Exclusion criteria included: (i) hypersensitivity to previous receipt of d-cycloserine per participant report; (ii) epilepsy or history of seizures; (iii) meeting DSM-IV criteria for alcohol or drug abuse in the past month or dependence in the past three months; (iv) active suicidal or homicidal ideation; (v) initiation or increase in dosage of any antidepressant within six weeks or mood stabilizer within four weeks; (vi) previous or current participation in cognitive remediation; (vii) current use of d-cycloserine; (viii) reduced kidney or liver functioning, B12 deficiency, folic acid deficiency, megaloblastic anemia; or sideroblastic anemia; (ix) current use of any medication known to have problematic interactions with d-cycloserine, including etionamide and isoniazid; (x) history of the blood disease porphyria; (xi) current active symptoms of psychosis defined as not meeting remission criteria for psychotic symptoms (Andreasen et al. 2005) using the Positive and Negative Syndrome Scale (Kay et al. 1987); (xii) evidence of dementia or other organic impairment that may reduce cognitive functioning; and (xiii) breastfeeding or pregnancy in female participants.

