### Randomization and treatment allocation

Treatment allocation of this study is depicted in Figure 1. Upon enrollment in the study, participants will be randomized using a 1:1 ratio to one of two study arms: (i) CR + DCS or (ii) CR + placebo. Randomization will be completed using a block randomization procedure with blocks of varying size. Both participants and study personnel will be blind with regard to participant assignment to either DCS or pharmacological placebo.

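### The stated power of at least 0.80 holds for f = 0.25, but in the G*Power routine that yields it, f = 0.25 is a large difference (1.0 single-visit SD), not a medium one

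*Protocol article*

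**What the plan says.** All references are to the protocol article.

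- **Primary outcome measure:** "the primary outcome measure will be change in the MCCB global cognition composite score from the baseline to 6-month assessment".
- **Participants:** "Approximately, forty individuals with bipolar disorder will be recruited to participate in this study".
- **Randomization and treatment allocation:** "participants will be randomized using a 1:1 ratio to one of two study arms".
- **Proposed analyses:** the time by treatment interaction on the MCCB composite "will be assessed using a repeated measures ANOVA". On power: "An a priori estimate of statistical power was completed using G*Power 3.1". Assuming a correlation of 0.40 or more between the two visits and "a medium effect size (i.e., *f* = 0.25), the power to detect a statistically significant interaction between time and treatment condition" is put at 0.80 or more.

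The article does not name the G*Power effect-size option and does not translate f into MCCB points or SD units. It states alpha of 0.05 only for the post-hoc t-tests.

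**The concern.** Calling f = 0.25 medium is the convention for comparing independent groups. With two groups f = d/2, so f = 0.25 means d = 0.5. A repeated-measures interaction f, standardised by the SD of a single visit with the correlation entered separately, is on another scale. The same 0.25 there stands for a difference twice as large.

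The label matters because it is the only description of the detectable effect that the article offers. Both arms receive the same cognitive remediation, so the contrast is what d-cycloserine adds to it. The Background also reports that, in the earlier schizophrenia trial, the arm given d-cycloserine showed no improvement on this composite. A reader who takes the power sentence at face value would credit the trial with more sensitivity to a moderate add-on effect than it has.

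**Working it through.** **Inputs.** N = 40, 20 per arm (Participants; 1:1 allocation). Two visits, m = 2 (Primary outcome measure). f = 0.25 and correlation ρ = 0.40, the stated floor (Proposed analyses). Assumed: two-sided alpha 0.05 for the interaction test, and no dropout. The power statement makes no allowance for dropout, and missing data are to be multiply imputed.

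**Step 1. Reproduce the stated power.** The default within-between interaction uses λ = N f² m / (1 − ρ), with 1 and N − 2 degrees of freedom:

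λ = 40 × 0.0625 × 2 / 0.6 = 8.33; F(1, 38); power = 0.803.

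The alternatives tried do not give 0.80:

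| G*Power variant | λ | Power |
|---|---|---|
| Default interaction option | 8.33 | 0.803 |
| Cohen option, f²N | 0.0625 × 40 = 2.50 | 0.338 |
| SPSS option, f²(N − 2) | 0.0625 × 38 = 2.375 | 0.324 |
| Between-factor routine, f²Nm/(1 + ρ) | 5/1.4 = 3.57 | 0.453 |

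Only the default matches. Quoting a correlation also fits it, since ρ enters there separately from f.

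**Step 2. Convert f = 0.25 to a difference in change.** Let D be the between-arm difference in change and SD the single-visit SD. In a 2 × 2 layout with equal arms, each interaction residual is ±D/4, so f = D/(4 SD). Cell means (0, 0) and (0, 1.0) in SD units leave residuals of ±0.25, hence f = 0.25. A difference of 0.5 SD gives f = 0.125.

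So f = 0.25 means D = 1.0 SD. The SD of change is SD × √(2(1 − ρ)) = 1.095 SD at ρ = 0.40, which makes D = 1/1.095 = 0.91 SD of change. At ρ = 0.70 the SD of change is 0.775 SD and the same D is 1.29 SD of change.

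**Step 3. Confirm through the equivalent test.** With two arms and two visits, the interaction F test is the two-sample t-test on change, with λ = (D/SD)² × (N/4) / (2(1 − ρ)). For D = 1.0 SD and ρ = 0.40, λ = 10/1.2 = 8.33, as in step 1. Simulating the t-test on change gave power 0.802.

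**Step 4. Power for a conventional medium difference, d = 0.5.**

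*Unit: SD of change.* λ = 0.25 × 10 = 2.5, power 0.338. The correlation does not enter.

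*Unit: single-visit SD.* λ = 0.25 × 10 / (2(1 − ρ)) = 1.25/(1 − ρ):

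| ρ | λ | Power |
|---|---|---|
| 0.40 | 2.08 | 0.29 (simulation 0.290) |
| 0.50 | 2.50 | 0.34 |
| 0.60 | 3.13 | 0.41 |
| 0.70 | 4.17 | 0.51 |
| 0.80 | 6.25 | 0.68 |
| 0.85 | 8.33 | 0.80 |

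**Step 5. Margin around 40.** The article says approximately forty. At N = 39, λ = 39 × 0.0625 × 2 / 0.6 = 8.125 and power for f = 0.25 at ρ = 0.40 is 0.793.

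**The case against.** The strongest reply is that no stated number is wrong. The inputs are f = 0.25, a correlation of at least 0.40 and about 40 participants, and they do give 0.803. The article also defines its own adjective: medium means f = 0.25, and power for d = 0.5 is nowhere promised. The first part stands. A reader might infer that the power claim is false on the plan's own inputs or that the sum was done wrongly; the documents do not support that. The second part does not rescue the label. If f is read on the scale where 0.25 is conventionally medium (the Cohen option), power is 0.338. The figure of 0.80 and the word medium do not hold together under any variant tried.

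A second reply is that 0.40 is a floor, so quoting only 0.29 to 0.34 for a medium difference is too narrow. This stands. The article gives no estimate of the correlation, and in single-visit SD units power rises with it. It is still below 0.80 until the correlation is about 0.85.

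A third reply is that reporting a confidence interval, or a rule for reading a non-significant result, belongs to a fuller plan. This also stands. A reader might infer that the trial intends to treat a null result as excluding a medium benefit. The article does not say so, and leaving such points out of a condensed protocol is not a fault.

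Finally, the G*Power option is an inference. It is a well-supported one, but the authors should confirm it.

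**Conclusion.** The point holds as a mislabelled effect size, not as an arithmetic error. Power of about 0.80 applies to a between-arm difference in MCCB composite change of 1.0 single-visit SD, which is 0.91 SD of change at correlation 0.40 and more at higher correlations. That is large, and twice the difference that the word medium conventionally denotes when both are measured in single-visit SDs. For a conventional medium difference, the power of this design is well short of the stated level across most plausible readings, and how far short depends on the SD unit and the correlation, as tabulated above.

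The conclusion rests on 40 participants split equally, two-sided alpha 0.05 for the interaction, no loss of information from dropout, and the inferred default option. It does not show that the sample size must change; it shows that the stated sensitivity is misdescribed.

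**What to change.** Keep the sample size, remove the word medium, name the G*Power option used, and restate the power sentence, for example:

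> With 40 participants (20 per arm), two-sided alpha 0.05 and a correlation of 0.40, power is about 0.80 (0.79 with 39 participants) for a between-arm difference in MCCB composite change of 1.0 baseline SD (interaction f = 0.25), a large effect. For a difference of 0.5 baseline SD, power is about 0.29 at a correlation of 0.40 and 0.51 at 0.70.

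This is a change of wording only. It needs no further participants or procedures and leaves the endpoint and test as they are. The cost is that the trial's declared sensitivity looks less favourable.

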Despite the apparent benefits of CR for individuals with serious mental illnesses, this intervention does not appear to completely ameliorate the cognitive deficits that accompany these illnesses. Consequently, there is growing interest in the use of pharmacological cognitive enhancers to increase the benefits of CR (Goff et al. 2011; Krystal et al. 2009; Chou et al. 2012). In such models, cognitive enhancers are not thought to promote improved cognition by themselves; rather they are hypothesized to augment the physiological mechanism(s) through which CR produces its therapeutic benefits (e.g., learning (Hofmann et al. 2011) or neuroplasticity (Cain et al. 2014)) One such promising cognitive enhancer is d-cycloserine (DCS)—a partial or full agonist of NMDA receptors (depending on the subunit composition of the receptor (Dravid et al. 2010)) that may facilitate the learning process for emotional and non-emotional information through the promotion of long-term potentiation (Assini et al. 2009; Lelong et al. 2001; Onur et al. 2010; Ressler et al. 2004). Of note, dysfunction in glutamate transmission, which is regulated in part by NMDA receptors, has been hypothesized to contribute to the cognitive dysfunction that accompanies bipolar disorder (Goldberg & Roy Chengappa 2009).

To date, several controlled trials have found that DCS augmentation can enhance the therapeutic benefits of learning-based psychosocial interventions for anxiety disorders (Norberg et al. 2008; Bontempo et al. 2012). However, we are unaware of any study that specifically examines the benefits of pairing DCS with CR for individuals with bipolar disorder. One recently completed trial examined whether a weekly dose of 50 mg DCS enhanced the benefits of CR among individuals with schizophrenia (Cain et al. 2014). This study found that subjects who received both DCS and cognitive remediation showed greater improvements in performance on an auditory discrimination task as compared to subjects who received cognitive remediation alone. Conversely, only subjects who received cognitive remediation alone experienced improvements in global cognition as measured using the composite score for the MATRICS Consensus Cognitive Battery (MCCB: (Nuechterlein et al. 2008)). Subjects who received both cognitive remediation and DCS showed no improvement in the composite or specific cognitive domain scores for the MCCB.

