#### Cognitive functioning: rate of improvement

Recent evidence raises the possibility that DCS may not increase the benefit received from participation in psychosocial interventions, but instead may help individuals achieve this benefit more quickly (Siegmund et al. 2011; Kushner et al. 2007; Wilhelm et al. 2008; Chasson et al. 2010). Thus, to assess the rate of improvement in cognitive functioning, participants will complete the Repeatable Battery for the Assessment of Neuropsychological Status (RBANS: (Randolph 1998)). This brief assessment battery measures five domains of cognitive functioning: (i) immediate memory; (ii) visuospatial and constructional skills; (iii) language; (iv) attention; and (v) delayed memory. With four alternative forms, the RBANS is designed specifically to reduce the practice effect associated with multiple administrations of a neuropsychological test. This assessment battery will be administered at baseline, Week 5, Week 14, and 6-month follow-up.

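### Bonferroni t-tests after the 2 × 2 interaction add no evidence on DCS versus placebo; a baseline-adjusted between-arm difference with its 95% CI would serve better and is more precise

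*Protocol article*

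**What the plan says.** Under the primary outcome heading, the protocol article fixes the endpoint: "the primary outcome measure will be change in the MCCB global cognition composite score from the baseline to 6-month assessment". Under Proposed analyses, the test is set out in two parts: "The interaction between time (i.e., baseline vs. 6-month) and treatment condition (DCS vs. placebo) on our primary outcome variable" (the MCCB composite) "will be assessed using a repeated measures ANOVA". Power of at least 0.80 is claimed for f = 0.25 and a baseline to 6-month correlation of at least 0.40. If the interaction is significant, "post-hoc probing of the interaction will be completed using t-tests with Bonferroni corrections to maintain an alpha of 0.05". The section does not say which t-tests are meant (between arms at each assessment, within each arm, or both) or how many share the alpha.

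The size and allocation come from the Participants section ("Approximately, forty individuals with bipolar disorder will be recruited to participate in this study") and the randomization section ("participants will be randomized using a 1:1 ratio to one of two study arms"), which gives about 20 per arm.

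**The concern.** Post-hoc probing is useful when an interaction has several degrees of freedom and the reader needs to know where the difference lies. Here there is one degree of freedom, and it already is the treatment effect on the primary outcome. The tests that could follow are different contrasts:

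- A between-arm test at 6 months ignores the baseline score and pays a Bonferroni penalty.
- A between-arm test at baseline compares randomised groups before treatment.
- Within-arm tests of change are not randomised comparisons. They include whatever gain both arms share from remediation and retesting.

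A reader shown a significant interaction and a non-significant corrected t-test may think the effect is unsupported. A reader shown a significant change in one arm only may take this as further support, although the arm comparison has already been made. The step also draws attention away from the estimate and its precision, which matter most in a trial of 40.

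**Working it through.** **Inputs.** From the article: N about 40, allocation 1:1 (n = 20 per arm), two assessments, f = 0.25, correlation ρ = 0.40. Assumed: two-sided alpha 0.05 for the interaction, normal scores, SD 1 at both assessments, complete data, and two or four follow-up tests.

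**1. The plan's own figure.** In the G*Power setting for a within-between interaction, λ = f² × N × m / (1 − ρ) = 0.0625 × 40 × 2 / 0.60 = 8.33. With df 1 and 38, power is 0.803. The stated power of at least 0.80 reproduces, and N = 40 is the smallest even total that reaches it.

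**2. What f = 0.25 means as a difference between arms.** The SD of change is √[2(1 − ρ)] = √1.2. The SE of the between-arm difference in change is √(1.2 × 2/20) = √0.12 = 0.346 SD. The implied difference is √8.33 × 0.346 = 2.887 × 0.346 = 1.00 SD.

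**3. The interaction is the treatment effect.** In a simulated data set with two arms and two assessments, the interaction F was 0.13658 and the squared two-sample t on change was 0.13658. They are the same test.

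**4. How often a follow-up test differs in significance.** Simulation of 100,000 trials per scenario, among trials with a significant interaction:

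| True difference | Interaction power | 6-month between-arm test non-significant, 2 tests (0.025) | 4 tests (0.0125) |
|---|---|---|---|
| 1.0 SD (planned) | 0.80 | 14% | 22% |
| 0.5 SD | 0.29 | 54% | 66% |

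The within-arm results depend on the change assumed in the placebo arm. At 1.0 SD with two tests, both arms change significantly in 2%, 8% and 29% of these trials for an assumed placebo-arm change of 0, 0.3 and 0.5 SD. All four t-tests fail together in at most 1.4% at the planned effect.

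**5. Change score against baseline adjustment.** By randomisation, a 1.00 SD difference in change is also a 1.00 SD expected difference at 6 months.

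- Change score: variance factor 2(1 − ρ) = 1.20; SE 0.346; half-width 2.024 × 0.346 = 0.70 SD; power 0.80.
- ANCOVA: variance factor 1 − ρ² = 0.84; SE = √(0.84 × 2/20) = √0.084 = 0.290; half-width 2.026 × 0.290 = 0.59 SD; noncentrality 1.00/0.290 = 3.45 on 37 df; power 0.92.

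The variance ratio is 0.84/1.20 = 0.70, which is (1 + ρ)/2. A simulation that also allows for chance baseline imbalance gave ANCOVA power of 0.91 and a mean half-width of 0.59 SD, so the approximation is close.

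**The case against.** The strongest reply is that nothing in the primary analysis is wrong. The interaction is the correct randomised contrast for the stated outcome. The t-tests run only after it is significant, so they cannot inflate its type I error or overrule it. Simple effects also tell the reader something the interaction does not: whether the DCS arm gained, the placebo arm declined, or both. All of this stands, and it limits the point to what the follow-up tests contribute to the arm comparison.

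Three stronger readings are tempting and are not supported.

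- A reader might infer that the trial's conclusion would rest on one arm improving and the other not. The Background reports an earlier schizophrenia trial in that form ("only subjects who received cognitive remediation alone experienced improvements in global cognition"), but it is describing another study. In this plan the between-arm test comes first.
- A reader might infer that the t-tests can contradict the primary result. They can be non-significant when it is significant, but they are different contrasts, the corrected 6-month test is less powerful, and there is no logical conflict.
- A reader might infer that a null result would be left without an estimate or interval. Only the probing depends on significance. The article is silent on intervals, and a condensed article commonly leaves these to the full protocol or SAP. That silence is no error.

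It is also fair to say that the 54% and 66% figures use half the planned effect, and that the article fixes neither the type nor the number of t-tests, so every discordance figure is conditional on an assumption.

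**Conclusion.** The point holds in limited form. The planned follow-up t-tests give no further evidence on DCS versus placebo and can differ from the interaction in significance: 14% to 22% of significant trials at the planned 1.0 SD effect for the 6-month comparison. They do not invalidate the primary test, and no figure in the article is wrong.

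The larger gain is available elsewhere in the same paragraph. Adjusting for the baseline MCCB score, which is already collected, reduces the variance of the treatment estimate by 30% at correlation 0.40. This is an improvement to a valid analysis, not the correction of an error. Its size rests on a correlation of 0.40, equal SDs, normal scores and complete data. Because the variance ratio is (1 + ρ)/2, the gain shrinks as the correlation rises.

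**What to change.** In Proposed analyses, replace the interaction test and its conditional t-tests with wording such as: *The treatment effect is the between-arm difference in the 6-month MCCB composite, adjusted for baseline MCCB composite (ANCOVA), reported with its 95% CI. Within-arm changes and differences at single assessments are descriptive.*

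The primary outcome can remain change in the composite, since with baseline as covariate the treatment estimate is the same whether the response is the 6-month score or the change. The power statement should be restated for the new analysis: a 1.0 SD difference, correlation 0.40, N = 40, complete data, power about 0.92 and expected CI half-width about 0.59 SD. The planned sample size, assessments and multiple imputation need not change. The cost is a few sentences of rewording, and within-arm p-values are no longer used for inference.
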